#### Inclusion criteria

2.2.1

Patients aged >18 years undergoing elective arthroscopic shoulder joint repairs admitted for a day surgical procedure, with the ability to provide informed consent.

#### Exclusion criteria

2.2.2

Not consenting; contraindications to spinal injections as per the American Society of Regional Anesthesia and Pain guidelines^[25]^; known allergy to LA; allergy to all opioid medications; diagnostic shoulder arthroscopic procedures; inability to understand or comprehend in English language; history of daily opioid medication use for the past 1 month; and patients with planned overnight hospital stay.

### Control of bias

2.3

#### Randomization

2.3.1

Treatment allocation will be done with an allocation ratio of 1:1 using a computer-generated variable block randomization using block sizes of 2, 4, and 6. This randomization list will be prepared by a statistician who is not involved with the study data analysis and provided to the hospital pharmacy. Randomization will happen on the day before surgery. Each patient will be designated a unique randomization code.

#### Allocation concealment

2.3.2

Study allocation will be performed by the pharmacy and will be concealed by having 2 sets of syringes with equal volumes marked as “for ESPB” and “for PAI” delivered to the operating room (OR) on the day of surgery, before the performance of the block for each patient. The solutions within the syringes will not have any identifiers, and hence will be completely concealed. These syringes will be used for the respective study interventions for each patient.

#### Achievement of blinding

2.3.3

Since the medication syringes contain clear solutions, and the study uses a double dummy technique for blinding by performing both interventions in each patient, patients, physicians, other healthcare providers, and data collectors are effectively blinded. Apart from the statistician who has prepared the randomization code and the pharmacist preparing the study medications, all other personnel are blinded for assessment and data analysis.

### Application of interventions

2.4

#### Intervention group

2.4.1

##### Active ESP block, saline PAI

2.4.1.1

The ESP block will be performed immediately before surgery, in a designated regional anesthesia block room. Intravenous (IV) access will be established and standard monitoring including noninvasive blood pressure, electrocardiogram, and pulse oximetry will be applied. Sedation and anxiolytics may be used as clinically appropriate. The block will be performed by anesthesiologists who have been trained to perform ESP and who do ESP on a regular basis. The patient will be placed in a sitting position and the area over the thoracic spine will be sterilized with disposable swabs of 2% chlorhexidine in 70% isopropyl alcohol and then draped in a sterile fashion. A high-frequency linear US transducer (GE. LOGIQe) will be placed in a longitudinal parasagittal orientation 3 cm lateral to the T2 spinous process. The trapezius, rhomboid major, and erector spinae muscles will then be identified superficial to the tip of the T2 transverse process. The patient's skin will be anesthetized with 2% lidocaine. A 17-gauge 8 cm needle (Arrow StimuCath; Teleflex Medical, Markham, Ontario, Canada) will be inserted using an in-plane superior-to-inferior approach to place the tip into the fascial plane on the deep (anterior) aspect of erector spinae muscle. The location of the needle tip will be confirmed by visible fluid spread lifting erector spinae muscle off the bony shadow of the transverse process. A total of 30 mL of 0.25% bupivacaine with 5 μg/mL of epinephrine will be injected in 5 mL aliquots through the needle (maximum of 3 mg/kg).

The orthopedic surgeon will perform saline PAI at the end of surgical procedure on the operated side rotator cuff. The surgeons will identify the desired area and advance the needle at an approximately 20° angle in the joint space. The PAI will be performed using a total of 30 mL of saline injected in 5 mL aliquots through the needle. Nurse-administered opioids will be initiated postoperatively in the PACU.

#### Control group

2.4.2

##### Saline ESP block, active PAI

2.4.2.1

The ESP block will be performed similar to above, but with 30 mL of saline injected as 5 mL aliquots, immediately before surgery. The orthopedic surgeon will perform an active PAI at the end of surgical procedure, on the operated side rotator cuff using 30 mL of 0.25% bupivacaine with 5 μg/mL of epinephrine injected in 5 mL aliquots. The procedure will be performed as described above.

#### The OR

2.4.3

Patients included in the study would be managed according to OR protocol. Study patients will be identified during the surgical “time out” period. The attending anesthesiologist responsible for the care of the patient will provide a general anesthetic as per the routine institutional practice. Both groups will have no restrictions on the anesthetic management except that any long-acting agent (morphine/hydromorphone) is administered at least 30 minutes before extubation, so that the PACU pain scores are comparable.

#### PACU and day surgery unit (DSU) protocol

2.4.4

All patients will be monitored in the PACU until they are transferred to DSU before their discharge. Standard order sets will be used for PACU and DSU analgesia. A research assistant will be present in PACU or DSU for all patients at all times. For both groups, nurse-administered IV opioids will be initiated in PACU similar to routine practice according to the order sets (choice of fentanyl, hydromorphone, or morphine). Pain scores will be appropriately recorded and pain scores at 30 minutes after PACU admission will be noted for analysis. Opioid analgesic administration will be individualized based on allergies, co-morbidities, and patient tolerance. Ketorolac will be used only as a rescue (30 mg IV) for pain score of >3/10 after 30 minutes (as appropriate based on allergy). At 30 minutes in PACU, patients will receive acetaminophen if they can tolerate by mouth (as appropriate based on allergy). Patients will be discharged home when DSU discharge criteria are met. Standardized prescriptions will be given to each patient based on individual allergies and comorbidities.

#### Follow-up

2.4.5

Study patients will be followed for 24 hours and at 1 month after surgery by a telephone call from a trained research assistant with a scripted set of questions. Participant flow is shown in Figure 1 (consolidated standards of reporting trials flow chart).

### Outcomes

2.5

#### Primary outcome and measurement

2.5.1

The primary outcome of this study will be to compare the resting pain scores after initial stabilization (30 minutes after admission) in PACU. Pain scores will be noted using the patient-reported numeric rating scale (NRS), an 11-point scale where 0 is no pain and 10 the worst pain imaginable.^[26]^ NRS is validated and considered easy to use.^[27]^

#### Secondary outcomes and measurement

2.5.2

The following secondary outcomes will be collected during the in-hospital stay and follow-up of study patients:

(1)Total opioid consumption in hospital (until discharge): opioid use will be converted into morphine equivalent dosage for analysis.(2)Pain intensity: pain scores with movement in PACU; pain scores at rest; and movement at readiness to discharge. Since patients will be asked not to move their shoulders by the surgical team, pain scores with movement will be collected by asking the patient to sit up from lying down position. Pain scores will be collected using the 11-point NRS scale.^[26]^ We will record the postoperative time of peak pain scores.(3)Safety outcomes: incidence of moderate to severe PONV and incidence of moderate to severe itching will be collected using validated scales^28^,^29^; incidence of ipsilateral diaphragmatic paralysis will be diagnosed using bedside US examination with sniff test,^[30]^ 30 minutes after admission. This has been observed to be valid and clinically feasible^[31]^; and incidence of respiratory depression^[32]^ and LA toxicity^[33]^ will be diagnosed based on clinical symptoms and signs. All these outcomes will be noted postoperatively in PACU and until discharge, unless specified.(4)Sensory blockade on the side of the operated shoulder: Sensory assessment of shoulder area will be performed by a trained research assistant. Sensory dermatomes corresponding to shoulder and upper arm and their blockade to cold sensation will be noted. In total we will observe sensory blockade in 7 dermatomal areas (Supplemental Digital Content (Appendix 1)) and compare the extent of blockade between the 2 groups by their median and range.^[34]^
(5)Patient satisfaction with postoperative analgesia: This will be recorded at hospital discharge and 24 hours and at 1 month after surgery (by a telephone call) and measured using a 7-item Likert scale.

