The erector spinae plane (ESP) block can be considered as a modification of the thoracic paravertebral block, which blocks thoracic spinal nerves using injections outside of the conventional paravertebral space.^[14]^ It was first described by Forero et al in 2016 in case reports of 2 patients of severe thoracic neuropathic pain as well as 2 cases of acute postsurgical pain following video-assisted thoracoscopic wedge resection and lobectomy.^[15]^ The ESP block demonstrated a unilateral cutaneous sensory block of the posterior, lateral, and anterior chest wall as well as relief of neuropathic pain in these cases.^[15]^ ESP block is performed under ultrasound (US) by injecting LA deep to the erector spinae muscle at the interfascial space between either the erector spinae muscle and the rhomboid major muscle (higher up), or between the erector spinae muscle and the external intercostal muscles, at lower sites.^[15]^ Cadaveric studies of US-guided ESP blocks with methylene blue dye and subsequent dissection, as well an ESP block with a dye mixture and computed tomography scanning demonstrated that when injecting deep to the erector spinae the block likely affects the ventral and dorsal rami leading to the sensory blockade.^[15]^ The advantages include its simplicity and safety by limiting the risk of nerve damage and pneumothorax.^15^,^16^ Subsequent case reports have demonstrated ESP to be effective for abdominal surgery,^17^,^18^ breast and axillary surgery,^[19]^ and open radical cystoprostatectomy with ureter and bladder reconstruction.^[20]^ Recent case reports have explored its potential use for shoulder surgery when performed at a higher level (such as T2-T3). Forero et al reported successful management of chronic shoulder pain without motor blockade, with ESP performed at T3 level.^[21]^ A case report demonstrated ESP block used for shoulder surgery in 3 patients with variable success for postoperative analgesia.^[22]^

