### Objectives

1.2

The primary objective of this study is to determine whether ESP block is superior to PAI for in-hospital postoperative analgesia among patients who have undergone arthroscopic shoulder surgical repair. This will be determined by comparing the resting pain scores after initial stabilization in the postanesthetic care unit (PACU).

Secondary objectives will be to compare:

(1)resting pain scores at discharge;(2)pain scores with movement in PACU and at discharge;(3)total opioid consumption in hospital;(4)incidences of postoperative nausea and vomiting (PONV), itching, ipsilateral diaphragmatic paralysis, respiratory depression, and LA toxicity in hospital;(5)sensory blockade assessment in PACU;(6)patient satisfaction at discharge,(7)average pain scores, persistent surgical site pain and opioid use at 24 hours and at 1 month postoperatively.

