#### Outcomes at 24 hours

2.5.3

Patients will be contacted by telephone the next day, 24 hours after surgery, to ask the following questions:

(1)What was your average pain score over the last 24 hours after discharge, on a scale of 0 to 10 (NRS)?(2)Rebound pain: Is the nerve block still providing pain relief? Yes or NoAt what time following the surgery did the block wear off?At what time following the surgery did you take your first dose of opioid?(3)Are you continuing to use opioids postoperatively? If yes, provide drug name, frequency, and amount over the past 24 hours.(4)Are you satisfied with your postoperative pain control (Likert scale 1–7)?

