### Risk assessment and protocol adherence

2.9

This trial does not entail any higher risk than the standard of care to patients. Medications of known benefit are used in clinically acceptable doses. Patients are managed using standard preoperative, OR, PACU, and DSU protocols. The ESP block will be performed by anesthesiologists competent with the block.

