## Discussion

3

This RCT examines ESP block versus PAI in patients undergoing shoulder arthroscopy and assesses differences in pain scores and opioid consumption, as well as in safety and other patient outcomes. It will allow physicians to make an evidence-based choice in recommending ESP block for shoulder arthroscopy, and will provide data regarding the safety profile of ESP block. The advantages of the study would be establishing efficacy of the ESP block for shoulder arthroscopy, which could include lower pain scores, less opioid consumption and better patient satisfaction in PACU, at discharge and at 1 month. This study will also help provide an estimate of the incidence of side effects and complications of the ESP block including PONV, pruritis, diaphragmatic paralysis, and LA systemic toxicity.

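### The Discussion promises data on the complications of the ESP block, but needle-related and post-discharge harms are not systematically collected

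*Protocol article*

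**What the plan says.** All references are to the protocol article.

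- **Safety outcomes.** Section 1.2 (Objectives) lists "incidences of postoperative nausea and vomiting (PONV), itching, ipsilateral diaphragmatic paralysis, respiratory depression, and LA toxicity in hospital". Section 2.5.2 repeats these five. It adds that "incidence of ipsilateral diaphragmatic paralysis will be diagnosed using bedside US examination with sniff test", 30 minutes after admission, and sets the window: "All these outcomes will be noted postoperatively in PACU and until discharge, unless specified".
- **Calls.** Section 2.5.3 begins "Patients will be contacted by telephone the next day, 24 hours after surgery, to ask the following questions". The questions cover pain, whether and when the block wore off, first opioid dose, current opioid use and satisfaction. The 1-month questions in section 2.5.4 cover persisting pain at the operated site, average pain, opioid use and satisfaction. Section 2.4.5 describes the calls as scripted.
- **Rationale.** The Introduction counts persistent neurologic complications and pneumothorax among the risks of the interscalene block. It says of ESP: "The advantages include its simplicity and safety by limiting the risk of nerve damage and pneumothorax".
- **Design.** Under the double dummy in section 2.3.3 every patient has both procedures. For controls, section 2.4.2.1 states: "The ESP block will be performed similar to above, but with 30 mL of saline injected as 5 mL aliquots". Section 2.4.1.1 gives the active arm a saline periarticular injection.
- **Promise.** The Discussion says the trial will supply data on the safety profile of ESP, and "This study will also help provide an estimate of the incidence of side effects and complications of the ESP block including PONV". That sentence goes on to name pruritus, diaphragmatic paralysis and LA systemic toxicity.
- **Risk statement.** Section 2.9: "This trial does not entail any higher risk than the standard of care to patients".

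**The concern.** The Discussion reaches further than the data collection. Safety profile and complications are broad terms. A reader of the Introduction will take them to include nerve injury and pneumothorax, since those harms are used to argue for ESP, yet neither is a listed outcome.

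Timing adds to the problem. Until discharge the research assistant is recording sensory blockade as an intended effect (section 2.5.2, item 4). Numbness from a working block and numbness from an injured nerve look the same at that point and separate only once the block has worn off. The 24-hour call asks when it wore off but not whether numbness or weakness remained. The 1-month call asks about pain at the operated site, which is neither a neurological question nor one about the T2 puncture site.

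At stake is what the trial can say about ESP safety. A report with no nerve injury or pneumothorax would show only that none was volunteered. Harms that are not asked about at the calls cannot be reliably recovered later.

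**Working it through.** **1. What is promised against what is collected**

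| Harm | Where it is raised | Collected as a stated outcome? |
|---|---|---|
| PONV | Discussion | Yes, to discharge |
| Itching | Discussion | Yes, to discharge |
| Diaphragmatic paralysis | Introduction, Discussion | Yes, ultrasound at 30 minutes |
| LA systemic toxicity | Discussion | Yes, to discharge |
| Respiratory depression | Sections 1.2 and 2.5.2 | Yes, to discharge |
| Rebound pain | Introduction | Yes, 24-hour call |
| Nerve injury | Introduction | No |
| Pneumothorax | Introduction | No |

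The window opens at different points in the two sections: in hospital in section 1.2, postoperatively in PACU in section 2.5.2. In both it closes at discharge.

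**2. What the shared puncture does**

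Both arms receive the ESP puncture with 30 mL. If the puncture carries a harm rate p, the expected difference between arms is p − p = 0 for any p. A between-arm comparison therefore carries no information on puncture harm. The incidence p can still be estimated by pooling the arms. The site of the active drug does differ between arms, so contrasts of drug effects are unaffected.

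**3. The plan's own figure**

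The protocol gives no precision for safety. Its sample size (section 2.6.1) is set for pain: difference 2, SD 2.5, two-sided alpha 0.05, 80% power.

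n = 2 × (1.960 + 0.842)² × 2.5² / 2² = 24.5, rounded up to 25 per group, as stated.

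At the final 30 per group the t-test power is 86.1%, in line with the stated 85%. The safety data therefore rest on 30 active-ESP patients, or 60 punctured patients in all.

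**4. Precision with zero events**

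Exact two-sided 95% upper limit = 1 − 0.025^(1/n).

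- n = 30: 1 − 0.025^(1/30) = 11.6%
- n = 60: 1 − 0.025^(1/60) = 6.0%
- n = 50 (if only the 25 per group of the base calculation were treated): 7.1%

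**5. Chance of at least one event**

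P = 1 − (1 − p)^n. The documents give no harm rates, so p is an assumption, shown over a range.

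| Assumed p | n = 30 | n = 60 |
|---|---|---|
| 0.1% | 3.0% | 5.8% |
| 0.5% | 14% | 26% |
| 1% | 26% | 45% |
| 2% | 45% | 70% |
| 5% | 79% | 95% |

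Pooling roughly halves the upper limit at no recruitment cost. Rare harms stay out of reach: at 0.1%, even 60 fully questioned patients would most likely show none.

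**6. The risk statement**

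Sections 2.3.3, 2.4.1.1 and 2.4.2.1 together give every participant one saline injection whose only purpose is blinding. For controls it is a 17-gauge needle placed in the erector spinae plane at T2. Section 2.9 does not mention this when it says that the trial adds no risk to standard care.

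**The case against.** The strongest reply has four parts.

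- **The named effects are covered.** All four effects listed in the Discussion are collected, and respiratory depression is added. When the Introduction explains why an alternative to the interscalene block is wanted now, it names diaphragm paralysis and rebound pain, and both are measured. This stands. A reader might infer that the trial cannot deliver the safety data it promises; for the named effects that is wrong. The gap lies in the wider terms and in the harms behind them.
- **The double dummy is sound.** It protects the blinding of a subjective primary outcome, and an incidence estimate needs no unpunctured control. This stands too. A reader might infer that the trial is set up to find no difference in complications whatever the puncture risk. No between-arm test of puncture harm is planned, so the shared puncture limits attribution and is not itself a defect.
- **The article condenses a longer protocol.** General adverse-event reporting may sit there, and a patient may volunteer a problem on a call. It would therefore be too strong to say that a late harm has no chance of being recorded. What can be said is that the stated outcomes and the printed questions do not solicit it.
- **The risk statement is a matter of wording.** A reader might infer that the ethics board or the patients were misinformed. Neither the ethics submission nor the consent form is shown, so the documents do not support that. The Introduction's remark that placebo injections can be considered unethical concerns an inactive comparator; here every patient also receives an active injection. What remains is that section 2.9 does not fit the design sections.

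**Conclusion.** The point holds in a limited form. The Discussion's terms go beyond what is collected: nerve injury and pneumothorax are not stated outcomes, the stated safety outcomes end at discharge, and neither call asks about harms. A lasting deficit would be hidden by the working block before discharge and not asked about afterwards.

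The primary outcome, its test and the between-arm contrasts of the listed effects are not affected.

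With systematic questions and no events, the trial could exclude puncture harm above 6.0% in 60 patients, against 11.6% if only the 30 active-ESP patients were counted. These limits assume that all 60 are punctured and answer the questions. The detection probabilities rest on assumed rates. Even after the change the trial could speak only to common harms, which is a further reason to moderate the Discussion.

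This is an inexpensive improvement that changes what can be concluded about ESP safety.

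**What to change.** 1. **Sections 2.5.3 and 2.5.4.** Add scripted questions to both calls on persisting numbness or weakness, new breathlessness or pneumothorax needing care, problems at the puncture site, and unplanned care.
2. **Section 2.5.2.** Keep the five present outcomes as a comparison between arms. List the puncture-related harms separately, reported descriptively in all patients who had the ESP puncture, as one pooled incidence with an exact two-sided 95% interval and no between-arm claim.
3. **Discussion.** Limit the statements on safety profile and complications to what is collected, and say that only common harms can be excluded.
4. **Section 2.9.** Reconcile the risk statement with sections 2.3.3, 2.4.1.1 and 2.4.2.1, under which each participant receives one saline injection solely for blinding.

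Cost: slightly longer calls, one descriptive table and a less favourable risk statement. No extra visit, staff or procedure is needed. The questions must be in the scripts before the calls are made.

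### Recording of local anesthetic toxicity (and possibly block-related respiratory depression) starts at PACU, after the active ESP injection but only shortly after the active PAI, although the objective covers the hospital stay

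*Protocol article*

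**What the plan says.** Four parts of the protocol article bear on this.

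- **Objective (section 1.2).** The fourth secondary objective compares, among other outcomes, "respiratory depression, and LA toxicity in hospital".
- **Measurement (section 2.5.2).** The safety item ends: "All these outcomes will be noted postoperatively in PACU and until discharge, unless specified". The only different timing within that item is the diaphragm ultrasound, set at 30 minutes after admission. LA toxicity and respiratory depression are to be diagnosed clinically, with no separate start time.
- **Timing of the injections (sections 2.4.1.1 and 2.4.2.1).** In the ESP arm, "The ESP block will be performed immediately before surgery, in a designated regional anesthesia block room", with bupivacaine; then "The orthopedic surgeon will perform saline PAI at the end of surgical procedure on the operated side rotator cuff". In the control arm the order is the same but the contents are swapped: the ESP injection is given "with 30 mL of saline injected as 5 mL aliquots, immediately before surgery", and then "The orthopedic surgeon will perform an active PAI at the end of surgical procedure, on the operated side rotator cuff", with bupivacaine.
- **Use of the data (section 3, Discussion).** "This study will also help provide an estimate of the incidence of side effects and complications of the ESP block"; LA systemic toxicity is among those listed.

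Section 2.8 names PACU, the day surgery unit and the time after discharge as the points of data collection. It does not name the block room or the operating room. Section 2.4.1.1 applies standard monitoring at the block, but nothing says that an event seen there is recorded as a trial outcome.

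**The concern.** The objective and the measurement rule give different windows, and the narrower one does not treat the two active injections alike. The double dummy gives every patient both needle procedures at the same two times, but the study bupivacaine goes in at the first time in one arm and at the second time in the other. A window that opens at PACU therefore opens late relative to active ESP and early relative to active PAI.

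For an outcome that depends on time since the bupivacaine injection, this matters in two ways. The ESP incidence that the article intends to report could be too low for the hospital stay. The comparison between arms could also lean toward the experimental block. Events that were never recorded cannot be recovered in the analysis.

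**Working it through.** **The plan's own figures.** The documents state no figure for the safety comparison. The only number that enters here is the 30 per group of section 2.6.1, which was set for the pain score. It raises no difficulty: 2 × (1.960 + 0.842)² × (2.5/2)² = 24.5, so 25 per group as stated. At 30 per group the noncentral t gives 86.1% power, against 85% stated.

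**Step 1: same active drug amount in both arms.** 30 mL × 2.5 mg/mL (0.25%) = 75 mg of bupivacaine in each arm. What differs between the arms is the site and the time of the active injection.

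**Step 2: time between active injection and the start of recording.**

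| Arm | Active injection | Not recorded after it | Recorded after it |
|---|---|---|---|
| ESP | Block room, before surgery | Rest of block-room stay, induction, whole operation, emergence | PACU and day surgery unit |
| PAI | End of surgery | End of surgery to PACU admission | PACU and day surgery unit |

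Neither arm is fully covered. The unrecorded stretch is longer in the ESP arm by roughly the length of the operation.

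**Step 3: which outcomes this touches.**

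- LA toxicity: affected, since it follows the drug injection.
- Respiratory depression: possibly affected, where it is caused by the block. It is hard to assess during general anesthesia, and block-room sedation can occur in either arm.
- PONV: postoperative by definition, so not affected.
- Itching: rated by the awake patient, so not clearly affected.
- Diaphragmatic paralysis: one ultrasound at the same fixed time in both arms, so not clearly affected.
- Needle-related harm: both arms undergo both procedures, so it is missed equally.

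**Step 4: direction and possible size.** Let fE and fP be the shares of LA-toxicity events that occur before PACU in the ESP and PAI arms. Then

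observed ESP incidence = true incidence × (1 − fE)

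observed RR (ESP/PAI) = true RR × (1 − fE)/(1 − fP)

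The documents give neither share, so the values below are assumptions. The true RR is set to 1.0.

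| fE | fP | Observed RR |
|---|---|---|
| 0.25 | 0 | 0.75/1.00 = 0.75 |
| 0.50 | 0 | 0.50/1.00 = 0.50 |
| 0.90 | 0 | 0.10/1.00 = 0.10 |
| 0.90 | 0.25 | 0.10/0.75 = 0.13 |
| 0.90 | 0.50 | 0.10/0.50 = 0.20 |

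The ratio falls below its true value whenever fE exceeds fP. If the shares are equal, the comparison is undistorted, although both incidences are still understated. If recording covers all the time from each active injection, fE = fP = 0 and the RR returns to 1.0, provided that events are detected equally well throughout.

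**Step 5: how many events are at issue.** At an assumed true risk of 1%, 30 × 0.01 = 0.3 events are expected per arm over the whole stay. At an assumed 5% it is 1.5 per arm; with fE = 0.50 and fP = 0, the recorded counts would be 0.75 against 1.5.

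**The case against.** The strongest reply is that the text is inconsistent rather than firmly tied to PACU. The objective covers the hospital stay, section 2.5.2 opens by referring to the in-hospital period, and the quoted rule allows for exceptions. Table 2, which lists the outcomes and their measurement, is not shown and may time each one. A condensed article may also leave adverse-event capture in the block room and operating room to the full protocol. This is a fair reason for caution about what will happen in practice. It does not remove the point: the article states a start, gives no exception for these two outcomes, and names collection sites that leave out the block room and the operating room.

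The reply also stands against several stronger readings that a reader might draw:

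- *That the safety comparison as a whole is biased.* Three of the five listed outcomes are not clearly affected, and needle-related harm is missed equally in both arms.
- *That the period after ESP is unobserved and the period after PAI is observed.* Later effects of ESP fall inside the window, and the minutes between PAI and PACU admission fall outside it.
- *That a zero count shows the size of the error.* No events in 30 gives a one-sided 95% upper limit of 1 − 0.05^(1/30) = 9.5% (two-sided, 1 − 0.025^(1/30) = 11.6%) whatever the window. It measures the imprecision of 30 patients, and section 2.6.2 plans no one-sided limit.

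Finally, 30 per arm cannot support a comparative conclusion on a rare event under either window. That lowers the weight of the point on the comparison. It does not answer the point on the stated aim of estimating ESP incidence.

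**Conclusion.** The point holds for LA toxicity and possibly for block-related respiratory depression. The objective and the measurement rule differ on the window. Followed as written, the rule leaves early drug reactions after active ESP uncounted while covering more of the period after active PAI. The likely direction is an understated ESP incidence and an LA-toxicity comparison that leans toward ESP. This rests on the assumption that a larger share of events precedes PACU in the ESP arm than in the PAI arm, which follows from the timing of the injections. The size cannot be derived: the risk ratios of 0.10 to 0.75 depend on assumed shares, and few events are expected.

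The documents do not support a general finding that the trial's safety results are biased. The primary outcome, the sample size and the primary analysis are unaffected. Severity is moderate to low.

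**What to change.** Reconcile sections 1.2 and 2.5.2 by replacing the general window for these two outcomes with a sentence such as: *LA toxicity and respiratory depression are recorded from the first study injection, including the block room and operating room, until discharge, with the same window in both arms, and are reported by period (block room, operating room, PACU/day surgery unit).* Leave the timing of PONV, itching and the diaphragm ultrasound as it is. Add the block room and operating room to the collection points in section 2.8.

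The cost is one protocol sentence, the matching entry in section 2.8 and one case report form line. The clinicians already present at the block and the operation, who are blinded under section 2.3.3, can complete that line. Treatment, visits and sample size do not change. There are two small downsides. The clinicians take on recording that section 2.8 now assigns to research assistants and nurses. Symptoms also cannot be reported under general anesthesia, so detection in the operating room will be incomplete; reporting by period keeps that limit visible.
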